These barriers have created substantial service gaps [17]. In addition, they have exacerbated treatment inequities, leaving young Black men involved in violence in underserved communities to adopt ineffective coping techniques, such as service avoidance or *opting out* [22]. Service avoidance takes the form of deliberate attempts to avoid or disengage from formal treatment or rehabilitation programs perceived to be associated with *feds* or that place them *in the system* [22], whereas *opting out* from preventative programs can manifest as early dropouts, noncompliance, nonparticipation, tardiness, and absenteeism even when the court system mandates program completion. Consequently, persistent service-avoidant behaviors contribute to violence recidivism, substance use relapse, and a revolving-door approach to prevention. Therefore, improving youth access to and trust in existing violence and substance use prevention interventions is critical.

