#### Phase 3—Clinical Trial

##### Overview

Overall, 60 young Black men (not part of phases 1 and 2) will be recruited to a single-group, pretest-posttest study of the finalized version of BrotherlyACT. This pilot test will determine its early feasibility outcomes (the feasibility of recruitment and retention methods; feasibility of module co-design with youth by observing fidelity to and deviations from the study protocol; completion of outcome measures; and satisfaction, appropriateness, cultural relevance, feasibility, and acceptability of the intervention). We will also ascertain the implementation outcomes for a large trial (ie, adherence, sustainability, and usability).

Assessments will be taken at baseline (T0) and after the intervention (T1) at 10 weeks, with SMS text message prompts to complete modules and study sessions. Given the exploratory nature of this study and its focus on feasibility, acceptability, and implementation outcomes, phase 3 data analyses will not be designed to have a specified level of statistical power. Nonetheless, with sample size of N=60, pretest-posttest correlation of 0.60, and α^2^ (tailed)=.05, we estimate 80% power to detect a pretest-posttest change of Cohen *d*≥0.33 (a small to medium effect). We will use mean imputation on the missing items in the event of participant loss. Participants who leave the study will be compared with those who stay to identify any differences in baseline and follow-up data for descriptive purposes and to determine if data are missing at random.

##### Data Analysis for Phase 3

Pretest and posttest scores will be compared to see if participants improved, stayed the same, or deteriorated on each outcome scale. Data will be checked for missing data patterns, distributions of outliers, and variable distributions to ensure that they meet the assumptions of planned analyses. For baseline characteristics, descriptive statistics will be generated. We are limited in attributing postintervention change without a control group to the intervention. Thus, the effects observed are preliminary. All statistical analyses will be conducted using SAS. Initial data analysis will be performed to check for data quality, including allowable ranges and errors.

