Generalized linear models will analyze the pretest and posttest survey measures using repeated measures analysis. As this pilot study is exploratory, we will use a *P* value <.05 to denote significant findings but not adjust for multiple tests, given the pilot nature of the study. Exploratory analyses will examine differences in rates of pretest-posttest change by baseline characteristics, including recruitment site (pediatric ED vs community). To test such moderation effects, terms for the moderator and for the moderator × time (before and after) interaction will be added to the models described previously. Significant interactions will be graphed to aid interpretation. At the end of the 10-week study period, participants will complete exit interviews via the web individually and will complete the SUS. Additional open-ended process interview questions will focus on young Black men’s perceptions of BrotherlyACT and the research experience. As part of this study, responses to exit interview questions will be recorded with permission and thematically analyzed in a qualitative phase before being combined with pretest and posttest findings.

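### Phase 3 takes the usability score and the perception interview only at week 10, so participants lost earlier give no rating and these user-rated results may be biased upward

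*Protocol article*

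**What the plan says.** In the protocol article, Methods, Phase 3—Clinical Trial, Overview, 60 young Black men "will be recruited to a single-group, pretest-posttest study of the finalized version of BrotherlyACT". The feasibility outcomes there include satisfaction, appropriateness, cultural relevance and acceptability, alongside "the feasibility of recruitment and retention methods" and completion of the measures. The implementation outcomes are adherence, sustainability and usability.

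Two assessment times are given: "Assessments will be taken at baseline (T0) and after the intervention (T1) at 10 weeks". Data Analysis for Phase 3 then fixes the user ratings: "At the end of the 10-week study period, participants will complete exit interviews via the web individually and will complete the SUS". The questions on how users saw the app belong to the same interview: "Additional open-ended process interview questions will focus on young Black men’s perceptions of BrotherlyACT and the research experience".

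For loss, the Overview plans mean imputation and a descriptive comparison of leavers with stayers. The Retention Plan adds at least three alternate contacts per participant and, in phase 3, periodic contact to check safety and update contact details. The article describes no rating between baseline and week 10 and none at early exit.

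**The concern.** A participant cannot rate an app before using it, so a baseline assessment cannot supply a usability or perception score. That leaves week 10. Anyone lost before then has no SUS and no interview.

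This matters because the reason for loss may be the thing being measured. A participant who finds the app confusing or does not trust it is more likely to disappear and would have scored it low. The article's own Introduction describes disengagement from prevention programs in this population, which "can manifest as early dropouts, noncompliance, nonparticipation, tardiness, and absenteeism even when the court system mandates program completion". It gives no rate.

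The pilot is meant to inform a definitive trial, and the authors expect the app to prove acceptable and usable. If the ratings come only from those still in contact at week 10, the faults that drive people away are the ones least likely to be seen. No later analysis can recover a rating that was never taken.

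**Working it through.** **1. The plan's own figure.** The only calculation in the phase 3 text is the power statement: "with sample size of N=60, pretest-posttest correlation of 0.60, and α^2^ (tailed)=.05", giving "we estimate 80% power to detect a pretest-posttest change of Cohen *d*≥0.33".

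- Standardised paired difference: dz = d / √(2(1 − r)) = 0.33 / √0.80 = 0.33 / 0.894 = 0.369.
- Paired t-test, n = 60, two-sided 0.05, noncentral t: power 80.3%. The stated 80% reproduces.
- It does so only if all 60 give week-10 data. With 54, 48, 42 or 36 completers, power at d = 0.33 is 75.9%, 70.7%, 64.6% or 57.6%.

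This figure concerns pretest-posttest scales. The SUS has no pretest, so the figure neither supports nor answers the present point.

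**2. Which results need a week-10 response.**

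| Result | Needs a week-10 response? | Can cover all 60? |
|---|---|---|
| Recruitment, retention, adherence, completion of measures | No | Yes |
| SUS (usability) | Yes, stated | Only if reached at week 10 |
| Perceptions of the app (exit interview) | Yes, stated | Only if reached at week 10 |
| Satisfaction, appropriateness, acceptability scales | Inferred: instruments not named, but only baseline and week 10 are given | Only if reached at week 10 |

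**3. Size of the bias.** Let p be the share lost, S the stayers' mean SUS and L the mean the leavers would have given. The mean over everyone enrolled is (1 − p)S + pL = S − p(S − L). The reported mean is S, so the bias is p × (S − L). The documents give neither p nor L, so both are assumed:

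| Share lost (of 60) | Gap 10 | Gap 15 | Gap 20 |
|---|---|---|---|
| 10% (6) | 1.0 | 1.5 | 2.0 |
| 20% (12) | 2.0 | 3.0 | 4.0 |
| 30% (18) | 3.0 | 4.5 | 6.0 |
| 40% (24) | 4.0 | 6.0 | 8.0 |

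If loss has nothing to do with the app, the gap and the bias are zero.

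**4. The same issue for a proportion.** Suppose about 80% of raters find the app acceptable (assumed). The bounds over all 60 count every leaver as a no, then every leaver as a yes:

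- 10% loss, 43/54: 43/60 to 49/60, or 72-82%.
- 20% loss, 38/48: 38/60 to 50/60, or 63-83%.
- 30% loss, 34/42: 34/60 to 52/60, or 57-87%.

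**5. Whether the planned safeguards help.**

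- *Mean imputation.* A leaver has answered no SUS item, so the only mean available is the stayers'. The result is (1 − p)S + pS = S, and the bias is untouched. Precision is overstated: with 42 of 60 observed, the sum of squares stays the same while the count rises, so the standard error shrinks by the factor √[(41 × 42)/(59 × 60)] = √(1722/3540) = 0.70.
- *Leaver-stayer comparison.* It can show whether leavers differed at baseline. It cannot show what they thought of the app.

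**The case against.** Several points on the other side stand.

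- *Stopping the app is not leaving the study.* A reader might infer that everyone who abandons the app never rates it. The text does not support that. The week-10 SUS and interview are for participants, not for active users, and are done over the web. The alternate contacts and periodic contact make it plausible that a non-user can be reached. Only loss to follow-up makes a missing rating certain.
- *The feasibility results as a whole do not rest on stayers.* A reader might also infer that they do. Recruitment, retention and adherence can be counted over all 60, and the Expected Findings section plans to set objective data beside subjective data. Heavy dropout would show directly. It would show that people left, though not why.
- *The SUS mark of 68 is not a phase 3 criterion.* It is set for the steering group's alpha testing in phase 2. For example, a completer mean of 72 with 30% loss and a 15-point gap gives 67.5 over all 60, but it would be wrong to read that as failing a pilot threshold, since none is stated.
- *Earlier testing looks for usability faults.* Alpha and beta testing precede the pilot. Those testers are experts and advisory board members in guided sessions, not participants using the app remotely for 10 weeks, so this reduces the concern without removing it.
- *The article is condensed.* The full protocol may contain a withdrawal procedure. If it already collects a rating at exit, most of this point falls away. The week-10 timing of the SUS and interview, however, is stated outright.
- *The Background passage on opting out concerns formal or mandated programs*, and the article argues that digital delivery may reduce avoidance. It supports a risk, not an expected rate.

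**Conclusion.** The point holds in a limited form. User-rated usability and perceptions are fixed at week 10, participants lost before then contribute nothing to them, and neither planned safeguard repairs this. The results may be biased upward, by the share lost times the stayer-leaver gap: 1 to 8 SUS points for assumed losses of 10-40% and assumed gaps of 10-20 points. The direction rests on leavers rating the app lower than stayers, which is plausible but not shown in the documents. It is a design weakness worth correcting before phase 3 data collection, because an analysis plan cannot supply the missing ratings afterwards. It does not invalidate the pilot.

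**What to change.** 1. Send the 10-item SUS and a few acceptability items by SMS or web link early, for example after the first module or at week 2, and repeat them at week 10.
2. Offer the SUS and the exit interview when a participant withdraws or stops using the app.
3. State that week-10 ratings are sought from all enrolled participants, whether or not they still use the app.
4. Do not mean-impute the SUS for those lost.
5. Report early, exit and week-10 ratings separately, each with the number of raters out of 60, and compare the early ratings of later leavers with those of stayers.

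The ratings should not be pooled into one last-available score: that would mix impressions after a single short module with impressions after 10 weeks.

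The cost is one added short questionnaire through channels already planned, and a second trigger for an interview already planned. Participant burden rises slightly, and early ratings reflect less exposure to the app.

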## Results

Phase 1 data collection began in September 2021. Phases 2 and 3 are scheduled to start in June 2023 and end in September 2024. The entire study is expected to be completed by the end of 2025.

## Discussion

### Expected Findings

Using a mixed methods study format, subjective and objective feasibility and acceptability data will be compared. This will ensure that survey data can be quantified and contribute to our qualitative understanding of the curriculum’s practicality and acceptability.

Few antiviolence technology-enhanced interventions exist, and even fewer studies have studied the acceptability, usability, and engagement of a life skills and mindfulness coaching intervention for co-occurring youth violence and substance use among young Black men. The extent to which existing technology-enhanced interventions are used for violence prevention has been limited to supporting the work of street outreach workers [86]. We expect that BrotherlyACT will prove to be acceptable and usable by young Black men affected by violence. Furthermore, findings from the development of BrotherlyACT will be useful for a future definitive trial. This trial will validate an expanded version of BrotherlyACT across clinical and community-based settings for young Black men in Chicago and other cities with a high prevalence of youth violence. Clinical outcomes will be determined after we evaluate how well BrotherlyACT works (ie, reduction in violence and substance use, perceived likelihood of involvement in violence and problematic behaviors, self-efficacies to plan for a positive future, use of ACT and life skills, and likelihood of using service options). The success of this intervention in different deployment contexts (eg, in a hospital vs a community setting or web-based vs face-to-face setting) will be evaluated as part of the implementation analysis. BrotherlyACT will be tested (1) with referred (vs recruited) young Black men, (2) with an organic deployment by service providers (vs research staff), and (3) in comparison with conventional care in future effectiveness trials.

On the basis of previous application of qualitative methods [34] and UCD [34,59,62], we anticipate that our study will highlight the benefits of technology-enhanced modalities for addressing motivation and self-efficacy to reduce and prevent co-occurring violence and substance use among at-risk young Black men. Studies so far support an association between substance use and violence [4,5], with a consensus that substance use can increase both the frequency and severity of violence [4-6]. A common substance implicated in violent experiences when misused is alcohol, with the suggestion that eliminating hazardous drinking would reduce general violence by 44% [5]. Such findings have led many researchers to focus on developing integrated intimate partner violence and substance use interventions [4-6].

However, this study is the first stage in developing and evaluating a technology-enhanced intervention for reducing co-occurring violence and substance use among Black boys and men aged 15 to 24 years in a high-violence setting. We are using an existing theory-driven and evidence-based intervention (ie, ACTV) that has been proven to reduce violence. This approach eliminates the need for expensive additional investments in developing a new intervention from other data sources, which may face significant feasibility issues and require considerable time. Extending ACTV to noninstitutionalized juvenile samples exposed to youth violence is a logical next step. Addressing our research objectives squarely will drive innovation in violence prevention and identify settings, conditions, and limitations for situations where digital solutions are inapplicable or even detrimental.

Furthermore, crime prediction technologies, digital surveillance tactics, and facial recognition software have all been known to target and penalize Blackness [86]. Therefore, we approach this study through a transformative justice lens, mindful of how technology affects Black communities. We hold ourselves and our team accountable in our quest for ethical and dignified technology-enhanced interventions. We remain responsible to young Black men, who will support this process and, eventually, use BrotherlyACT.

### Strengths and Limitations

This study and our approach have some limitations. As our study only includes young Black men, we cannot generalize our results to other groups of young men (such as Hispanic; tribal; and lesbian, gay, bisexual, transgender, queer, and more youth) who are disproportionately affected by violence and substance use. Furthermore, using a single sample group for pretest and posttest will not infer causative relationships and will limit the causal attribution related to the proposed intervention. However, our goal at this stage is to develop and pilot-test BrotherlyACT for preliminary feasibility and acceptability. We have evaluated the power of our sample size using suggestions and guidelines for conducting pilot studies contained in the existing literature.

Nevertheless, it is possible that our sample size is very small, which could influence the results we receive. Regarding cultural adaptation of the intervention to young Black men, it can be challenging to present diverse groups with a unified view of *culture*. Some participants may find that traditional values conflict with their convictions or that generic cultural values may not adequately capture the particulars of their own cultural experience. Therefore, we intend to develop BrotherlyACT’s architecture to be adaptable to user requirements and capable of rapid, iterative adjustments. Moreover, young Black men who have perpetrated violence and use illicit substances are a self-selecting population that may not feel comfortable reporting their substance use and histories of violence, thus necessitating the use of novel recruitment tactics.

### Conclusions

At the individual level, studies show that life skills are a vital tool and coping strategy for adolescents in high-trauma contexts. Life skills have been used for decades to prevent violence and aggression in adolescents, particularly those in their early to middle adolescence. However, there is compelling evidence that low-income urban youth have few opportunities to observe, learn, or practice the actionable skills required to deal with the heightened levels and severity of the stressors they face. Accordingly, there is a need for combining multilevel strategies, such as psychoeducation and safety planning (at the individual level), with service engagement at the community level. There is also a dire need for easily accessible and youth-endorsed interventions that allow young people to acquire and practice these abilities as they plan for a values-based life. Improving Black adolescents’ access to skill-building resources and connecting them to already existing and trusted services is a critical and urgent public health need, the absence of which has resulted in a revolving-door approach to youth violence and substance use prevention.

## Appendix

Multimedia Appendix 1 Assessment, Decision, Administration, Production, Topical, Experts, Integration, Training, and Testing framework.

## Abbreviations

ACT: acceptance and commitment therapy
ACTV: Achieving Change Through Values-Based Behavior
ADAPT-ITT: Assessment, Decision, Administration, Production, Topical, Experts, Integration, Training, and Testing
BrotherlyACT: Boosting Violence-Related Outcomes Using Technology for Empowerment, Risk Reduction, and Life Skills Preparation in Youth Based on Acceptance and Commitment Therapy
CBT: cognitive behavioral therapy
ED: emergency department
IRB: institutional review board
REACH: Strategies to Recruit, Engage, and Retain Children in Behavioral Health Risk Factor Studies
REDCap: Research Electronic Data Capture
SUS: System Usability Scale
UCD: user-centered design
YCAB: youth and community advisory board
